### Interim analysis and stopping rules

There are no formal interim analyses planned for this trial. The DSMC periodically reviews data for the primary outcome measure and safety, and advises the chair of the management committee if, in their view, the randomised comparisons have provided both (i) ‘proof beyond reasonable doubt’ that one of the active arm interventions (CIAT Plus or M-MAT) is clearly superior or clearly inferior to usual care or because of safety concerns and (ii) evidence that might influence future patient management. The DSMC are guided by Haybittle-Peto boundaries in making this determination. That is, they work on the principle that a difference of at least 3 standard errors in the analysis of effectiveness or serious adverse events may be needed to justify halting or modifying the study before the planned recruitment is completed.

### Trial profile

The trial will be reported in accordance with the CONSORT statement for non-pharmaceutical trials and the COMPARE therapeutic protocol conforms to the SPIRIT statement. The report will include the number of screened patients who met the inclusion criteria, the number included, and the major reasons for exclusion of eligible patients. At follow-up, the number of patients withdrawn, lost to follow-up and the number who died within that period will be reported (see Fig. 1.).

**Fig. 1 Fig1:**
[figure not shown]
CONSORT flow diagram

### Patient characteristic and baseline comparisons

Baseline participant and stroke characteristics will be presented for each of the three groups: CIAT Plus, M-MAT and UC (Table 1). These will include age, gender, geographic region (Australia/NZ), living arrangements, stroke type, stroke severity (mRS) [15], and time since stroke. Baseline aphasia severity (WAB-R-AQ) [7], aphasia type (WAB-R-AQ) [7], apraxia of speech severity (ASRS) [16], naming (COMPARE naming battery) [8], attention (TEA) [17], memory (Visual Span) [18], non-verbal reasoning (Raven’s Coloured Matrices) [19], drawing (WAB-R Part 2) [7], praxis (WAB-R Part 2) [7], and communication efficiency (CIUs/minute) [9] will be presented in Table 2.

**Table 1 Tab1:** Baseline participant and stroke characteristics

	CIAT Plus *n* (%)	M-MAT *n* (%)	UC *n* (%)	All *n* (%)
Recruitment region				
Australia				
New Zealand				
Age, median (IQR)				
< 55				
55–70				
> 70				
Gender				
Male				
Female				
Non-binary/non-disclosed				
Time post most recent stroke onset (months), Median (IQR)				
Handedness				
Right handed				
Left handed				
No preference				
Living arrangements during study				
Home alone				
Home with other				
Supported accommodation				
Baseline mRS				
Low (0–2)				
High (3–6)				
Stroke type				
Haemorrhagic				
Infarct				
Infarct and haemorrhagic				
Unknown

**Table 2 Tab2:** Baseline speech, language and cognition characteristics

	CIAT Plus *n* (%)	M-MAT *n* (%)	UC *n* (%)	All *n* (%)
**Apraxia of Speech Rating Scale**				
No impairment				
Mild impairment				
Moderate impairment				
Moderate/severe impairment				
**Western Aphasia Battery-Revised-Aphasia Quotient**				
Above cut-off (93.7–100)				
Mild (62.6–93.6)				
Moderate (31.3–62.5)				
Severe (0–31.2)				
**Western Aphasia Battery-Revised Reading, Writing, Drawing, Praxis Subtests**				
Writing, mean (SD)				
Reading, mean (SD)				
Drawing, mean (SD)				
Praxis, mean (SD)				
**COMPARE Naming Battery,** mean (SD)				
**Communication accuracy and efficiency**				
No of CIUs, mean (SD)				
% CIUs per minute, mean (SD)				
**Communicative Effectiveness Index**, Mean (SD)				
**Scenario Test**, mean (SD)				
**Stroke and Aphasia Quality of Life Scale-39 g**				
Energy, mean (SD)				
Physical, mean (SD)				
Communication, mean (SD)				
Psychosocial, mean (SD)				
**Test of Everyday Attention**				
Elevator Counting, mean (SD)				
Visual Elevator, mean (SD)				
**Picture Span Memory Test**				
Pictures forward, mean (SD)				
Pictures backwards, mean (SD)				
**Raven’s Progressive Matrices**, mean (SD)				
**Self-rated Fatigue,** mean (SD)				
**Self-rated Distress,** mean (SD)				

Discrete variables will be summarised as frequencies and percentages. Unless otherwise indicated in the tables, percentages will be calculated according to the number of participants for whom data are available. If there are more than 5% missing values, the denominator will be indicated in the corresponding summary table. Continuous variables will be summarised by the mean and standard deviation (SD) or by the median and interquartile range (IQR). Durations and time intervals will be summarised by medians and IQRs.

### Primary outcome: reduction in aphasia severity immediately post intervention

#### Primary outcome measure

The primary outcome is reduction in aphasia severity immediately post intervention. Aphasia severity will be measured by the WAB-R-AQ [7]. The WAB-R-AQ [7] is a comprehensive measure incorporating production of spoken language and auditory comprehension.

#### Statistical hypothesis

The primary research hypothesis is that compared to UC, both CIAT Plus and M-MAT will result in reduced aphasia severity on the WAB-R-AQ [7] immediately post intervention. This will be tested by refuting the following null hypotheses: (a) there is no difference in aphasia severity, between the group receiving CIAT Plus and the group receiving UC immediately post intervention, and (b) there is no difference in aphasia severity, between the group receiving M-MAT and the group receiving UC immediately post intervention.

### Treatment of missing values

The primary analyses will be based on the intention to treat principle, that is, all participants will be analysed in the arm to which they were randomised. The primary analysis will be reported without imputation of missing data. If the amount of missing data warrants imputation (i.e. the number of missing values exceeds 10%), missing data imputation will be conducted under the assumption that missing values are missing at random (MAR). That is, it is assumed that the values of the missing data may reasonably be predicted from all observed data. In particular, it will be assumed that missing values of the primary outcome measure (WAB-R-AQ at intervention end) may be estimated from variables on which data has been collected (e.g., baseline aphasia severity, baseline stroke severity, age, gender, lesion size and location), and on the observed values of WAB-R-AQ. To ensure robustness of the imputation, 20 imputed data sets will be generated with a separate model being developed for each imputation. These multiple imputations will be conducted using chained equations. The pooled result of these imputed models will be reported and compared with the primary model (without imputed data). Based on monitoring by the DSMC, 6% of the data for the primary outcome measure in the COMPARE trial is missing at the time of publication of the statistical analysis plan. Sensitivity analyses that consider various other plausible assumptions about missing data will be presented.

### Analysis method

The primary aim of this trial is to compare the effects of CIAT Plus and M-MAT to usual care. This will be achieved through the primary effectiveness hypothesis which will be analysed using a linear mixed effects regression model with WAB-R-AQ as the outcome measure. Each intervention group will be compared to the UC group on the primary outcome measure (WAB-AQ immediately post intervention). The model will adjust for differences in baseline aphasia severity and baseline stroke severity by including the baseline WAB-R-AQ and the baseline mRS as covariates in the model. The effect of conducting therapy in groups will be controlled for by including the treatment group as a random effect. The treatment effect will be reported as difference in WAB-R-AQ with the corresponding 95% confidence interval.

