### Randomisation

Eligible participants are randomised to one of three arms: CIAT Plus, M-MAT, or UC. The intervention protocol requires therapy to be provided face-to-face, in groups of three participants. The members of a treatment group therefore need to be in the same geographic location. The trial uses a stratified group-randomisation strategy. Once enrolled in the trial, participants are allocated to treatment groups based on their aphasia severity (WAB-R-AQ mild = 93.7–62.6; moderate = 62.5–31.3; severe < 31.3). The groups are then randomised to one of three arms (M-MAT, CIAT Plus or UC) in a 1:1:1 ratio via a central allocation system using blocked randomisation within each stratum.

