### Sample size considerations

The study is powered to detect a difference of 5 points on the WAB-R-AQ [7] at therapy completion. Although the minimal clinically important difference for the WAB-R-AQ [7] has not been formally determined, the standard error of measurement for participants with chronic aphasia is 4.33 points [21] with a 5-point difference considered clinically meaningful [22]. We used this information to estimate the required sample size in two steps. First, we conducted a naïve power analysis (which did not account for the clustering effect of conducting therapy in groups) which indicated a sample size of 198 to achieve 80% power at the 5% significance level. In the second step, we adjusted for the clustering effect of group therapy since the outcomes of participants from within the treatment cluster may be correlated. We anticipated a relatively small intraclass correlation coefficient (ICC) of 0.04. This is consistent with estimates of ICC used in other studies, where prior information on the size of the intraclass correlation was not available. Based on this intraclass correlation coefficient and a group size of 3, we calculated a maximum design effect of 1.08. To adjust for the clustering effect, we multiplied this value by the design effect, and rounded off to a multiple of 3, to obtain balanced allocation across the three treatment groups. This yielded the required sample size of 216.

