### Analysis methods

*Comparison of CIAT Plus and M-MAT with UC immediately post intervention and 12 weeks: Aphasia Severity (WAB-AQ), Efficiency of Connected Speech (CIUs/min), Functional Communication (CETI), Multimodal Communication (Scenario Test), and Quality of Life (SAQOL-39 g).*

Longitudinal linear mixed models will be used to compare each of the CIAT Plus and M-MAT groups to the UC group on WAB-R-AQ, CIUs/min, CETI, Scenario Test and SAQOL-39 g at therapy completion and 12 weeks. The between-group differences will be assessed through a *group × time* interaction effects. The models will adjust for baseline aphasia severity by including the WAB-R-AQ at baseline as a covariate. Baseline stroke severity will be controlled for by including mRS at baseline as a fixed factor in the models. The treatment group will be included as a random effect.

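### The comparisons with usual care leave out the severity band used to form and randomise groups; adding it is a nearly free safeguard against standard errors that may otherwise be too wide

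*SAP article*

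**What the plan says.** The Randomisation section of the SAP article cuts WAB-R-AQ into mild, moderate and severe bands. Groups of three are formed within a band and then randomised "in a 1:1:1 ratio via a central allocation system using blocked randomisation within each stratum".

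The primary model (section Analysis method) adjusts for severity by "including the baseline WAB-R-AQ and the baseline mRS as covariates in the model". On clustering it says: "The effect of conducting therapy in groups will be controlled for by including the treatment group as a random effect".

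The longitudinal models against UC (section Analysis methods) do the same for WAB-R-AQ, CIUs/min, CETI, Scenario Test and SAQOL-39 g: "The models will adjust for baseline aphasia severity by including the WAB-R-AQ at baseline as a covariate". There mRS is called a fixed factor, and therapy group is again random.

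Neither section lists the band. Only the section comparing CIAT Plus with M-MAT brings in severity classes, through a group-by-severity interaction.

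On clustering, Sample size considerations says: "We anticipated a relatively small intraclass correlation coefficient (ICC) of 0.04".

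**The concern.** The band is constant within a therapy group. Any difference between band means that the AQ term does not capture therefore looks to the model like variation between groups. It raises the fitted group variance and ICC, and so the standard error of each comparison with UC. Blocked randomisation within bands has already balanced that variation across arms, so the estimate itself does not become more variable. The model would then report more uncertainty than the design leaves.

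Some departure from a single line is plausible. The trial's own sixth secondary hypothesis expects the ranking of the two active treatments to reverse in the moderate band. In the secondary models, AQ is also the only language-severity adjuster for outcomes on other scales. At stake are precision and power in the UC comparisons, because 216 is only just above the calculated requirement.

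**Working it through.** **The plan's own figure.** Design effect = 1 + (3 − 1) × 0.04 = 1.08. Then 198 × 1.08 = 213.84, and the next multiple of 3 is 216. This reproduces. It gives 72 participants, or 24 groups of three, per arm.

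**Implied SD.** The plan states none. Solving 66 = 2 × (1.960 + 0.842)² × SD² / 5² gives SD = 10.25 (10.18 with the t distribution). An SD of 6 is used as a lower assumption, since adjustment for baseline AQ reduces the residual SD.

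**Formula.** With 24 groups of three per arm,

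SE² = (2/24) × (between-group variance + within-group variance / 3).

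Take three equally frequent bands and let the middle band lie *d* points off the line through the outer two. A model without the band then adds *d*² × (1/3) × (2/3) to the between-group variance.

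SD 10.25, ICC 0.04:
- Between-group variance 0.04 × 105.1 = 4.20; within-group variance / 3 = 0.96 × 105.1 / 3 = 33.64.
- *d* = 0: SE = √(37.84 / 12) = 1.78.
- *d* = 5: add 25 × 2/9 = 5.56; SE = √(43.40 / 12) = 1.90, which is 7% wider.

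SD 6, ICC 0.04:
- Between-group variance 1.44; within-group variance / 3 = 11.52.
- *d* = 0: SE = √(12.96 / 12) = 1.04.
- *d* = 5: SE = √(18.52 / 12) = 1.24, which is 19–20% wider.

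**Simulation.** 72 groups of three, arms balanced within bands, true ICC 0.04, REML with a random group intercept, mRS left out, 600 runs per case. The table shows the excess of the model SE without the band over the model SE with it, for equal bands.

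| Assumed departure from the AQ line | SD 10.25 | SD 6 |
|---|---|---|
| none (linear) | −0.2% | −0.3% |
| smooth curve, 5 points down at the ends | 1.1% | 3.3% |
| smooth curve, 10 points down at the ends | 4.5% | 12.7% |
| middle band 2 points off | 0.8% | 2.7% |
| middle band 5 points off | 6.2% | 19.0% |
| middle band 10 points off | 26% | 66% |

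With 4, 6 and 14 groups per arm in the severe, moderate and mild bands, the 5-point step costs 4.5% and 13.9%. A separate run that only clipped scores to 0–100 showed no loss: SE 1.696 without the band and 1.698 with it (SD 10.2), and 1.028 and 1.030 (SD 6).

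**Is the wider SE real uncertainty?** No. For the 5-point step at SD 6, the model SE without the band was 1.25 against an empirical SD of 1.07. The fitted ICC was 0.17 (0.05 in the linear case) and type I error was 2%.

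**Power.** Assume gains of 3, 7 and 2 points in the severe, moderate and mild bands, the same in all arms (*d* = 7 − 2.5 = 4.5). The model SE is then 1.87 and the true spread 1.78. Power for 5 points is Φ((5 − 1.96 × 1.87) / 1.78) = Φ(0.75) = 77%, against 80% with the band. Gains of 2, 10 and 3 (*d* = 7.5) give SE 2.05 and power of 71%, against 81% in simulation.

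**The case against.** The strongest reply is that the band carries no information beyond the AQ score from which it is cut, and that score is in both models. Only departure from the fitted AQ term can reach the random effect. This stands, and it makes the loss conditional.

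Three further points also stand:
- A bounded scale alone is not evidence of loss, since clipping at 0–100 costs nothing.
- The larger losses need step gains shared by all arms. In the 2/10/3 case, moderate UC participants would gain 10 points over a two-week period, in chronic aphasia and with little or no therapy. When the same gains are given to the active arms only, the SE excess at SD 10.2 falls from 5.0% to 2.1% (3/7/2) and from 14.7% to 6.1% (2/10/3).
- A band main effect does not remove arm-by-band differences, which are the only band differences that the plan hypothesises.

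It can also be said that the article never states a straight line and may leave the functional form to the full SAP. That is fair as to form. A single covariate, set beside mRS as a fixed factor, is still most naturally read as one slope, and the terms that are listed do not include the stratification factor.

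A reader might infer that the error bars will be too wide and that the stated 80% power will be missed. The document does not support this: it gives no SD, no gains by band and no evidence of non-linearity.

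**Conclusion.** The point holds as an efficiency safeguard. The UC comparisons omit the factor that formed the groups and stratified their randomisation. The consequence ranges from nothing to a conservative test: there is no bias and no inflation of type I error.

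The SE excess is about 0% if the outcome is linear in AQ or merely bounded, 1–4% for a moderate smooth curve, and about 5–19% for a step of roughly 5 points in the middle band. These figures rest on an assumed SD of 10.2 down to 6, a true ICC of 0.04, assumed shapes and band mixes, and a single post-treatment score. The loss was not simulated for CIUs/min, CETI, Scenario Test, SAQOL-39 g or the longitudinal model, so no size is claimed there. Adjusting for the continuous score alone is a legitimate analysis that can be improved at almost no cost.

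**What to change.** In Analysis method (primary outcome) and in Analysis methods (longitudinal comparisons with UC), add the severity band as used for allocation as a fixed factor. Keep continuous baseline WAB-R-AQ, mRS and the random therapy-group effect.

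This takes one sentence in each section, and the variable is already needed for the CIAT Plus versus M-MAT model. It uses two degrees of freedom and raises the SE by about 0.2–0.3% if the relation is linear. The change should be fixed before outcomes are analysed by arm. If that point has passed, report the model with the band as a labelled sensitivity analysis.

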#### Secondary hypotheses

The following secondary hypotheses will be assessed:
Compared to UC, CIAT Plus and M-MAT will result in a reduction in aphasia severity on the WAB-R-AQ [7] at 12-week follow-up.Compared to UC, CIAT Plus and M-MAT will result in significantly more accurate and efficient connected speech (CIUs [9] per minute) immediately post intervention and at 12-week follow-up.Compared to UC, CIAT Plus and M-MAT will result in significantly better functional communication (CETI [10]) immediately post intervention and at 12-week follow-up.Compared to UC, CIAT Plus and M-MAT will result in significantly better multimodal communication (Scenario Test [11]) immediately post intervention and at 12-week follow-up.Compared to UC, CIAT Plus and M-MAT will result in a significantly better quality of life (SAQOL-39 [12]) immediately post intervention and at 12-week follow-up.M-MAT will be more effective in reducing aphasia severity (WAB-R-AQ [7]) immediately post intervention and at the 12-week follow-up than CIAT Plus for mild and severe aphasia, whereas CIAT Plus will be more effective than M-MAT for moderate aphasia.

#### Secondary statistical hypotheses

The specified set of secondary effectiveness hypotheses involve the assessment of the following statistical hypotheses:
1.1.CIAT Plus will result in greater reductions in aphasia severity than UC, as measured by the WAB-R-AQ [7], at 12 weeks post stroke.1.2.M-MAT will result in greater reductions in aphasia severity than UC, as measured by the WAB-R-AQ [7], at 12 weeks post stroke.2.1.CIAT Plus will result in better efficiency of connected speech than UC, measured by CIUs/min [9], immediately post intervention and at 12 weeks follow-up.2.2.M-MAT will result in better efficiency of connected speech than UC, measured by CIUs/min [9], immediately post intervention and at 12 weeks follow-up.3.1.CIAT Plus will result in better functional communication than UC, measured by the CETI [10], immediately post intervention and at 12 weeks follow-up.3.2.M-MAT will result in better functional communication of connected speech than UC, measured by the CETI [10], immediately post intervention and at 12 weeks follow-up.4.1.CIAT Plus will result in better multimodal communication than UC, measured by the Scenario Test [11], immediately post intervention and at 12 weeks follow-up.4.2.M-MAT will result in better multimodal communication than UC, measured by the Scenario Test [11], immediately post intervention and at 12 weeks follow-up.5.1.CIAT Plus will result in better quality of life than UC, measured by the SAQOL-39 [12], immediately post intervention and at 12 weeks follow-up.5.2.M-MAT will result in better quality of life than UC, measured by the SAQOL-39 [12], immediately post intervention and at 12 weeks follow-up.6.1.For participants with severe aphasia at baseline, M-MAT will result in greater reduction in aphasia severity than CIAT Plus, as measured by the WAB-R-AQ [7], immediately post intervention and at 12 weeks follow-up.6.2.For participants with moderate aphasia at baseline, CIAT Plus will result in greater reduction in aphasia severity than M-MAT, as measured by the WAB-R-AQ [7], immediately post intervention and at 12 weeks follow-up.6.3.For participants with mild aphasia at baseline, M-MAT will result in greater reduction in aphasia severity than CIAT Plus, as measured by the WAB-R-AQ [7], immediately post intervention and at 12 weeks follow-up.

### Analysis methods

*Comparison of CIAT Plus and M-MAT with UC immediately post intervention and 12 weeks: Aphasia Severity (WAB-AQ), Efficiency of Connected Speech (CIUs/min), Functional Communication (CETI), Multimodal Communication (Scenario Test), and Quality of Life (SAQOL-39 g).*

Longitudinal linear mixed models will be used to compare each of the CIAT Plus and M-MAT groups to the UC group on WAB-R-AQ, CIUs/min, CETI, Scenario Test and SAQOL-39 g at therapy completion and 12 weeks. The between-group differences will be assessed through a *group × time* interaction effects. The models will adjust for baseline aphasia severity by including the WAB-R-AQ at baseline as a covariate. Baseline stroke severity will be controlled for by including mRS at baseline as a fixed factor in the models. The treatment group will be included as a random effect.

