### Comparison between CIAT Plus and M-MAT groups WAB-R-AQ

A longitudinal linear mixed model will be used to assess the difference between the CIAT Plus and M-MAT groups on WAB-AQ immediately post intervention and at 12 weeks follow-up. The interaction effect: *group × baseline severity* will be included in the model to assess the effects of CIAT Plus and M-MAT on participants with different baseline severity classifications. The between-group difference at each time point will be assessed through the *group× time* interaction effect. The model will adjust for baseline aphasia severity by including the WAB-AQ at baseline as a covariate. Baseline stroke severity will be controlled for by including mRS at baseline as a fixed factor in the model. The treatment group will be included as a random effect.

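### The secondary longitudinal models judge arm differences by group × time, which on the two outcome times named is the change in the difference, not the difference at either time

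*SAP article*

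**What the plan says.** Under Analysis methods, the SAP article fits longitudinal linear mixed models that compare each active arm with usual care "on WAB-R-AQ, CIUs/min, CETI, Scenario Test and SAQOL-39 g at therapy completion and 12 weeks". It then states: "The between-group differences will be assessed through a" group × time interaction. On baseline it states: "The models will adjust for baseline aphasia severity by including the WAB-R-AQ at baseline as a covariate". Baseline mRS is a further fixed factor and the treatment group is a random effect.

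The section comparing CIAT Plus with M-MAT on WAB-R-AQ uses the same structure, adds a group × baseline severity term, and is more explicit about the target: "The between-group difference at each time point will be assessed through the *group× time* interaction effect".

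The hypotheses these models serve are listed under Secondary statistical hypotheses. A typical one reads: "CIAT Plus will result in better efficiency of connected speech than UC, measured by CIUs/min [9], immediately post intervention and at 12 weeks follow-up". Hypotheses 1.1 and 1.2 concern the 12-week time only. Hypotheses 2.1 to 6.3 concern both times. None is about how the arm difference changes between the two times.

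**The concern.** When the outcome is modelled at two times and baseline is a covariate, a group × time interaction measures whether the treatment effect changes between those times. It does not measure whether there is an effect at either of them. A therapy that helps equally at completion and at 12 weeks has an interaction of zero. A therapy that helps and then loses its whole effect has a large one.

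Followed literally, the plan would therefore report a sustained benefit as no evidence of a between-arm difference. It would be most likely to report significance when the benefit had gone by 12 weeks. The statistic named would not answer the hypotheses it is assigned to.

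**Working it through.** **What the interaction is.** Let d(post) and d(12) be the adjusted differences between an active arm and usual care at the two times. With post intervention as the reference time, the arm coefficient is d(post) and the arm × time coefficient is d(12) − d(post). The 12-week difference is the sum of the two coefficients. There is one interaction coefficient per active arm, so it cannot stand for two time-specific differences.

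**Inputs from the article (Sample size considerations; Randomisation).** Difference 5 points; two-sided 5% level; 80% power; naive total 198; ICC 0.04; groups of 3; allocation 1:1:1; final total 216. The article gives neither an SD nor a correlation between the two follow-up times.

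**Reproducing the plan's sample size.** Design effect = 1 + (3 − 1) × 0.04 = 1.08. Then 198 × 1.08 = 213.84, which rounds up to 216 as a multiple of 3, or 72 per arm. The stated figure reproduces.

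**Implied SD.** With 198/3 = 66 per arm, SD = 5 / (1.960 + 0.842) × √(66/2) = 10.25. This is a back-calculation that assumes a pairwise comparison of two arms.

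**Standard errors.** Effective number per arm = 72/1.08 = 66.7. For the arm difference at one time, SE = 10.25 × √(2/66.7) = 1.78. For the interaction, SE = 1.78 × √(2(1 − r)), where r is the correlation between the two times. This gives 1.78, 1.38 and 0.79 for r = 0.5, 0.7 and 0.9.

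**Chance of a significant result** (normal approximation, two-sided 5%):

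| True effect (post, 12 weeks) | Contrast at post | Contrast at 12 weeks | Interaction, r = 0.5 / 0.7 / 0.9 |
|---|---|---|---|
| 5, 5 | 80% | 80% | 5% / 5% / 5% |
| 5, 2.5 | 80% | 29% | 29% / 44% / 88% |
| 5, 0 | 80% | 5% | 80% / 95% / 100% |

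**Check by simulation.** With 24 groups of 3 per arm, ICC 0.04, SD 10.25, r = 0.7 and 20,000 runs, effects of (5, 5) gave 78% at each time and 5% for the interaction. Effects of (5, 0) gave 79% at post, 5% at 12 weeks and 96% for the interaction.

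**The case against.** The strongest reply is that the text itself aims at time-specific differences. The CIAT Plus versus M-MAT section refers to the difference at each time point, the Analysis methods section uses the plural for the interaction effects, and the general principles promise treatment effects with 95% confidence intervals. A single interaction coefficient per active arm cannot deliver that. The authors may therefore have meant contrasts taken from a model that contains the interaction, or interaction coefficients measured against baseline as the first level of time.

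The baseline reading has some support. The section on baseline and follow-up assessments counts baseline among the assessments the analysis needs. For CIUs/min, CETI, Scenario Test and SAQOL-39 g, the outcome's own baseline is not named as a covariate. With baseline as a level of time, each interaction coefficient would be the arm difference in change from baseline to that time. That is a valid test of hypotheses 2.1 to 5.2, so this part of the reply stands.

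The rest does not. Neither reading is written down, and the two sections name the interaction itself as the means of assessment. For WAB-R-AQ, making baseline a level of time would put it in the model both as a response and as a covariate. This is also more than detail that an article may leave to a fuller document, because the article names the statistic.

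A reader might go further and infer that none of secondary hypotheses 1 to 5 can be answered. The article does not support that: for the four outcomes other than WAB-R-AQ the defect depends on which levels of time were intended. A reader might also expect the interaction to reject far less often than 5% under a constant effect, because the treatment group is the only random effect named. That would come from leaving out a participant effect, which is a separate matter of covariance structure. A valid test of the interaction rejects at 5%.

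**Conclusion.** Wrong as written, for the secondary longitudinal models. The defect is firm for WAB-R-AQ (hypotheses 1.1, 1.2 and 6.1 to 6.3). For the other four outcomes it holds if time has only the two follow-up levels, which are the only ones the article names.

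Under a constant 5-point benefit the stated statistic would be significant in about 5% of trials, against about 78–80% for the contrast at each time. If the benefit vanished by 12 weeks, the statistic would be significant in about 80–100%. These figures rest on the implied SD of 10.25, ICC 0.04, 72 per arm and assumed correlations of 0.5 to 0.9. The 5% under a constant effect depends on none of these, since the interaction is then exactly zero.

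A reader might infer that the trial's main conclusion is at risk. It is not: the primary analysis compares each active arm with usual care directly, immediately post intervention, with baseline adjustment and no interaction. The sample size of 216 is not in dispute either.

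**What to change.** In both sections, state the levels of time and keep group × time in the model. Replace the sentence naming the interaction as the assessment with one that bases each secondary hypothesis on the model-estimated adjusted arm difference at post intervention and at 12 weeks, each with a 95% CI. With post as the reference time, these are the arm coefficient, and the arm plus arm × time coefficients. Interpret the interaction itself only as a description of durability.

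For hypotheses 6.1 to 6.3, take the contrasts within severity stratum. The two-way terms now listed give these only if the severity effect on the arm difference is the same at both times. Otherwise a group × severity × time term is needed, and the plan should say which applies.

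The cost is SAP wording. Apart from that possible extra term, the contrasts come from the model already planned, with no new data. The Summary reports that follow-up is complete and data lock is near, so the choice should be fixed before any analysis by arm.
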